### Who will take informed consent? {26a}

SPIRIT guidance: Who will obtain informed consent or assent from potential trial participants or authorized surrogates, and how (see Item 32). Details are provided in the ‘Study setting {9}’ section above.

### Additional consent provisions for collection and use of participant data and biological specimens {26b}

Not applicable as no additional consent provisions for collection and use of participation data and biological specimens will be collected as part of this trial.

## Interventions

### Explanation for the choice of comparators {6b}

Outcome and process imagery exercises will be chosen as the standard variants used in mental imagery intervention studies applied to physical health behaviours. A combination condition (i.e. outcome and process exercises presented in sequence) will be included to test (a) whether synergies between imagery exercises affected study outcomes and (b) to assess effects of intervention length on study outcomes. The health message control condition will be included on the basis that this is the standard visual/verbal health promotion warning encountered by UK citizens during the pandemic from July 2020 to the time of writing this protocol.

### Intervention description {11a}

The mental imagery intervention described in this protocol consists of two distinct imagery exercises—an ‘outcome imagery’ exercise and a ‘process imagery’ exercise. The complete text for the imagery intervention imagery conditions is included as an online supplementary resource. All imagery materials and written exercises will be hosted via an online questionnaire. Participants will be randomized to one of four conditions (outcome imagery; process imagery; outcome and process imagery; control ‘face covering warning’ condition). Each participant randomized to one of the three imagery exercise conditions will engage in an imagery exercise presented in three sequential parts. In part 1, participants will receive information about wearing face coverings in indoor public places. Specifically, imagery condition participants will read the following text defining face covering use in the context of the COVID-19 pandemic: ‘In the context of the coronavirus (COVID-19) outbreak, a face covering is something which safely covers the nose and mouth. You can buy reusable or single-use face coverings. You may also use a scarf, bandana, religious garment or hand-made cloth covering but these must securely fit round the side of the face’. In part 2, participants will be asked to visualize themselves wearing a face covering where this is required by UK law (i.e. in indoor public places). The importance of imagining distinctive, personally relevant visual imagery will be underscored in the passage providing instructions to all imagery condition participants. In part 3, participants will be asked to write about the mental images associated with the imagery exercise that they have completed. As detailed above, completion of imagery exercises is estimated to take approximately 8–12 min in total for single imagery interventions and between 15 and 25 min in total for combined imagery condition participants (i.e. those individuals completing both outcome and process imagery exercises).

#### Outcome imagery condition

Outcome imagery condition participants will be asked to visualize themselves successfully wearing a face covering in all required public places/situations over the coming week, and to imagine how they would feel (i.e. positive outcomes of having successfully worn face coverings where required to do so). Outcome imagery participants will then be asked to write in a free-text box how they would feel having successfully worn a face covering in required indoor public places/situations over the week ahead.

#### Process imagery condition

Process imagery condition participants will be asked to visualize the kinds of strategies involved in successfully wearing a face covering in all required public places/situations over the coming week. Process imagery participants will then be asked to write in a free-text box about the kinds of strategies that would be involved in successfully wearing a face covering in all required indoor public places/situations over the coming week.

#### Combined imagery condition

A third experimental condition will receive both outcome and process imagery exercises to read and complete in sequential order. The sequence will be ‘outcome exercise’ followed by ‘process imagery’ for all combined imagery condition participants. Following this sequence for all participants in this condition is based on the rationale that to imagine factors involved in successfully wearing face coverings where required it is intuitive to have first reflected on potential advantages/positive outcomes of doing so.

#### Control condition

A fourth condition will involve viewing a UK Government public health message circulated on social media as an image concerning the importance of wearing face covering while in public places. This message will be selected as a representative online message available on social media (https://twitter.com/GOVUK/status/1286304635767140352) in early August 2020 at which time the intervention was under development. The image is representative of UK Government public health guidance on wearing face coverings in public places during the COVID-19 pandemic at this time [8].

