**Methods:**

The primary objective of this randomized controlled study is to assess the effectiveness of a mental imagery intervention on wearing face coverings, as a defined core COVID-19 preventative behaviour. Participants will consist of UK university students and university employees of any age. Participants will be randomized to complete an ‘outcome imagery’ or a ‘process imagery’ exercise, both exercises (i.e. a combined condition) or neither exercise (i.e. a control condition). A total of 260 individuals will be recruited into the study. Outcomes for all study condition arms will be assessed at baseline (Time 1), immediately post-intervention (Time 2), and at 1-month follow-up (Time 3).

The primary outcome is frequency of wearing face covering, as reported at T2 and T3. Secondary outcomes include intervention effects on face covering attitudes, social norms, perceived behavioural control and barrier self-efficacy at T2 and T3. Putative moderators of intervention effects are conscientiousness, narcissism and ‘light triad’ personality traits.

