### Objectives {7}

#### Goals and objectives

Drawing on recent meta-analytic conclusions which have substantiated the value of mental imagery interventions in the context of health behaviours [19] and a template approach for preparing rigorously developed, well designed mental imagery interventions [25], we planned to develop a theory-based behavioural intervention to promote face covering adherence, and more favourable social cognitions toward face covering adherence, among UK university employees and students. Individuals recruited will be randomly assigned to one of four separate conditions (outcome imagery, process imagery, both outcome and process imagery, control). Participants assigned to an imagery condition will be provided with information about the defined COVID-19 preventative target behaviour; will be asked to visualize themselves wearing a face covering; and will be requested to record specific features of imagery generated during the imagery exercise in written form. The control condition will receive a health warning message drawn from a pool of standard/representative UK government messages alone (representing a ‘usual care’ face covering warning control condition). Study measures will be taken at three time points: at baseline prior to randomization (i.e. Time 1, T1 hereafter); immediately post intervention (i.e. Time 2, T2 hereafter); and at 1-month follow-up (i.e. Time 3, T3 hereafter). The time interval between T1 and T2 will vary depending on intervention condition but will last approximately 15–20 min. The primary goal of this randomized controlled trial (RCT) is to evaluate the efficacy of a mental imagery intervention designed to promote face covering adherence on face covering behaviour at T3. The secondary goal of this RCT is to evaluate the efficacy of the imagery intervention on social cognitions at T2 and T3.

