#### Design

An experimental, prospective design will be adopted. Participants will be randomized to one of four conditions (outcome imagery; process imagery; outcome and process imagery; control ‘face covering warning’ condition). Mental imagery interventions will be evaluated against the control condition immediately post-intervention (T2) and at 1-week follow-up (T3). The evaluation will adopt a 2 (outcome imagery vs no outcome imagery) × 2 (process imagery vs no process imagery) × 3 (time: T1, T2, T3).

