## Statistical methods

### Statistical methods for primary and secondary outcomes {20a}

#### Planned statistical analyses

Across T1–T3, Mean/SD values will be reported for behaviour and the psychological variables and percentages (of total sample) will be reported for demographic variables. Hypotheses stated previously will be tested via a series of ANCOVAs. Intervention condition will be a between-participants variable (outcome, process, combined, control) and time will be a within-participants variable (T1, T2, T3). The primary outcome (face covering behaviour) and secondary outcomes (intention, attitude, subjective norms, PBC, barrier self-efficacy) will be assessed as separate dependent variables. A factorial superiority framework will be adopted for this trial. This approach is preferred to a parallel group trial because it will permit testing for superiority of assignment to a specific imagery exercise technique (e.g. outcome imagery), regardless of study condition, rather than comparing simple assignment to one of the four conditions. Consistent with previous mental imagery interventions, demographic variables will be included as covariates. Where statistically significant effects are demonstrated from ANCOVA analyses, simple effects analyses will be conducted from which estimated marginal means will be reported for all primary and secondary outcome variables. The alpha level will be set at 0.01 for all analyses to control for Type I error rates. Moderation effects of personality traits (conscientiousness, narcissism, Faith in humanity, Kantianism, Humanism) on study intervention effects will be assessed using the PROCESS software macros (V.3.4) on IBM SPSS (V.26).

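### The control cell of the 2×2 carries its own message and the imagery cells carry their own information text, so the factorial main effects and interaction do not isolate imagery technique, synergy or length

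*Protocol article*

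**What the plan says.** The Design section sets out a "2 (outcome imagery vs no outcome imagery) × 2 (process imagery vs no process imagery) × 3 (time: T1, T2, T3") evaluation. Planned statistical analyses prefers a factorial superiority framework to a parallel-group one because "it will permit testing for superiority of assignment to a specific imagery exercise technique (e.g. outcome imagery), regardless of study condition". The abstract labels the fourth cell "neither exercise (i.e. a control condition").

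That cell does receive something. Goals and objectives states: "The control condition will receive a health warning message drawn from a pool of standard/representative UK government messages alone". The Control condition section agrees: "A fourth condition will involve viewing a UK Government public health message circulated on social media as an image".

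For the other arms, Intervention description {11a} states: "Each participant randomized to one of the three imagery exercise conditions will engage in an imagery exercise presented in three sequential parts". The parts are information on face coverings, visualization and writing. The government message is not among them.

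Explanation for the choice of comparators {6b} gives the combined arm two purposes: to test (a) "whether synergies between imagery exercises affected study outcomes and (b) to assess effects of intervention length on study outcomes". Section {11a} puts the exercises at 8–12 min for a single one and 15–25 min for the combined arm. The Combined imagery condition section fixes one order, outcome then process.

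**The concern.** A 2×2 main effect or interaction can be read as the effect of the named factors only if the four cells differ in nothing else. Here, as described, the no-imagery cell has a component of its own and the three imagery cells share a different one. An effect of either component enters both main effects and the interaction, and an analysis cannot remove it, because allocation to cells fixes it.

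At stake is what the trial may conclude. A main effect could be reported as the effect of a technique, and an interaction as synergy, when part of each is the difference between two pieces of information. The synergy and length aims also rest on the same arm, which differs from the single-exercise arms in content, duration and sequence together.

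**Working it through.** **The plan's own figure.** Sample size {14} gives a minimum of 254 for f = 0.25, power 0.80, alpha 0.01 and six covariates. A noncentral F calculation with four groups and 3 numerator df returns N = 254 (power 0.802). With 1 numerator df, as for a 2×2 main effect or interaction, it returns 191. The stated N thus fits an overall four-group test. It does not bear on the confounding, but it limits which power statements can be made.

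**Inputs.** Cell contents come from Goals and objectives, Intervention description {11a}, Combined imagery condition and Control condition. Let a and b be the effects of outcome and process imagery, ab their true interaction, m the effect of the message and i the effect of Part 1 information. Part 1 is assumed to be shown once per imagery participant. Means relative to a cell that receives nothing:

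| Cell | Mean |
|---|---|
| Control | m |
| Outcome | a + i |
| Process | b + i |
| Combined | a + b + ab + i |

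**Main effect of outcome imagery** = ½[(a + i) + (a + b + ab + i)] − ½[m + (b + i)] = a + ab/2 + (i − m)/2. By symmetry, process imagery gives b + ab/2 + (i − m)/2.

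**Interaction** = (a + b + ab + i) − (a + i) − (b + i) + m = ab + (m − i).

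There are six unknowns (baseline, a, b, ab, m, i) and four cell means. If message and information went to all four arms, both would cancel, leaving a + ab/2, b + ab/2 and ab.

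**Size.** The documents give neither m nor i, so these values are assumptions (SD units, ab = 0):

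| m | i | Shift in each main effect, (i − m)/2 | Interaction estimated, m − i |
|---|---|---|---|
| 0.1 | 0 | −0.05 | +0.1 |
| 0.2 | 0 | −0.10 | +0.2 |
| 0.3 | 0 | −0.15 | +0.3 |
| 0.2 | 0.2 | 0 | 0 |
| 0 | 0.2 | +0.10 | −0.2 |

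**Simple contrasts.** Imagery arm minus control gives a + i − m, b + i − m, and a + b + ab + i − m. Each is a whole imagery package against the usual-care message, which is the comparison that H1–H3 name.

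**Length.** Taking control as 0 min, suppose length acts linearly.
- With exact doubling (0/10/10/20 min), the interaction contrast is 20 − 10 − 10 + 0 = 0 and each main-effect contrast is ½(10 + 20) − ½(0 + 10) = 10 min. Length loads entirely on the main effects.
- At the extremes of the stated ranges, the interaction contrast is 25 − 2×8 = +9 min or 15 − 2×12 = −9 min, so some length can enter the interaction.
- A non-linear length effect, or an order effect, enters the interaction in any case.

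No contrast among the four cells isolates length from imagery content.

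**The case against.** **A usual-care message is a legitimate comparator, deliberately chosen.** This stands. The hypotheses compare imagery with control, and none concerns the interaction. The problem is confined to the factorial reading and the two aims given for the combined arm, but the protocol commits to both.

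**The message may be shown to every arm.** The full intervention text is in a supplement not shown here, and the word alone in Goals and objectives could mean message only versus message plus imagery. The listed components favour the reading taken above without settling it.

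**Both components may be weak.** Section {6b} calls the message the standard warning that UK citizens had met since July 2020. The definition quoted for Part 1 is also supplied within the questionnaire scales (Psychological measures). Either effect may be small, but the protocol does not establish this. A fresh effect would matter most for the cognitions measured at T2; the primary outcome is behaviour at one month.

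**A stronger conclusion is tempting.** A reader might infer that both imagery effects are understated, that synergy is overstated, and that power suffers badly: with i = 0, N = 260, a true effect of 0.5 SD and a 1-df test, power falls from 92% at m = 0 to 59% at m = 0.3. The documents do not support this. The direction depends on i − m, which is unknown, and the stated N fits a 3-df test, so these are not the trial's planned power figures. Nor does length necessarily contaminate the interaction: under a linear effect with exact doubling it does not.

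**Conclusion.** The point holds as a limit on interpretation. As the arms are described, the factorial main effects are not clean effects of a technique and the interaction is not a clean measure of synergy. The distortion is (i − m)/2 on each main effect and m − i on the interaction, of unknown sign and size. The negative shifts tabulated above hold only if i = 0; equal effects would cancel.

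Synergy and length cannot both be read from the combined arm. Length falls on the main effects if linear with exact doubling, and otherwise at least partly on the interaction, where order effects also fall.

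This rests on two assumptions: the imagery arms did not see the message, and Part 1 was shown once per participant. If the combined arm saw Part 1 twice with additive effect, the interaction would be ab + m and the main effects a + ab/2 + i − m/2 and b + ab/2 + i − m/2, which are still not clean. The H1–H3 contrasts against the usual-care message are unaffected.

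**What to change.** Trial status reports that enrolment ended on 28 February 2021, so for this trial the change is to the analysis description and reporting:

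1. Make the contrasts of each imagery arm with the message control the basis for efficacy claims under H1–H3.
2. Describe each factorial main effect as relative to a mix of conditions that includes the message control.
3. Do not interpret the interaction as synergy.
4. Drop the length aim in {6b}, or state that it is not identifiable.
5. If the supplement shows that all arms saw the message, say so in Goals and objectives, Intervention description {11a} and Control condition.

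The cost is wording, plus giving up the synergy and length conclusions.

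In any repeat, show the same message and the same Part 1 information in all four arms. This adds little material, and the question becomes imagery added to the usual message instead of imagery in place of it. It would not separate synergy from length or order, so item 4 would still apply.

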### Criteria for discontinuing or modifying allocated interventions {11b}

Not applicable as the intervention set-up did not require the facility for participants to be discontinued or for allocated interventions to be modified as part of this trial.

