## Assignment of interventions: allocation

### Sequence generation {16a}

After participants have completed complete demographic, psychological and behavioural measures at baseline (T1) they will be randomized to the outcome imagery exercise, the process imagery exercise, a combined condition (comprising the outcome and process imagery exercises) or a control condition. The allocation ratio (i.e. the ratio of participant numbers in each of the conditions) is intended to be equal across groups (i.e. 1:1:1:1). Throughout the recruitment period, the protocol author will conduct biweekly checks to audit that roughly equal allocation of participants to conditions has occurred. Randomization will be conducted via a Qualtrics randomizer features embedded in the T1 survey. The Qualtrics randomizer uses a Mersenne Twister pseudorandom number generator approach which is a widely used approach employed within standard statistical packages (e.g. IBM SPSS, Microsoft Excel). This approach follows a random method by which the randomization sequence cannot be determined until participant assignment has occurred while ensuring roughly even distribution of participants across groups. The researcher team will be blind to group assignment at the point of randomization.

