## Trial status

Enrolment for this study began on 19 August 2020 and ended on 28 February 2021. The total number of participants recruited includes a sample with complete data at T1/T2 only (*n* = 465) and a sample with complete data at T1 and T3 (*n* = 297). This study protocol is Version 2.0, dated 9 September 2020.

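### Full questionnaire completion is an eligibility criterion known only after randomisation, while task length before T2 differs by arm, so a completers-only comparison may favour imagery

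*Protocol article*

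**What the plan says.** All references are to the Protocol article.

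- **Randomisation.** Sequence generation {16a} places it after the baseline measures: "Randomization will be conducted via a Qualtrics randomizer features embedded in the T1 survey". Goals and objectives puts T2 immediately after the intervention.
- **Task between randomisation and T2.** For control: "A fourth condition will involve viewing a UK Government public health message". For the imagery arms, Intervention description {11a} gives "approximately 8–12 min in total for single imagery interventions and between 15 and 25 min in total for combined imagery condition participants". Those times cover reading, visualising and writing. Writing is the last step only: "In part 3, participants will be asked to write about the mental images associated with the imagery exercise that they have completed".
- **Stopping.** Item 11b: "Not applicable as the intervention set-up did not require the facility for participants to be discontinued or for allocated interventions to be modified". Items 11c and 18b plan no measures to support adherence or retention.
- **Who counts.** Eligibility criteria {10} include completion of the full questionnaire. The Participants section likewise makes completing the questionnaires a selection criterion.
- **Incomplete responders.** Plans for assessment and collection of outcomes {18a} says forced responses mean no data will be missing. It then plans an intention-to-treat analysis of all participants, including those with incomplete or absent follow-up, as an addition to complete case.
- **Numbers.** Trial status says the recruited total "includes a sample with complete data at T1/T2 only" (n = 465) and one with complete T1 and T3 data (n = 297).

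**The concern.** A criterion that is met or failed only after allocation cannot select participants neutrally if the arms differ in how hard it is to meet. Here they do: one image in control, one exercise in each single arm, two in the combined arm. A longer task gives more opportunity to close the survey.

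The protocol itself supplies the likely link to outcome. Its Background expects conscientious people to wear face coverings more, and H4 makes conscientiousness a moderator. If conscientious people also finish longer tasks more often, which is plausible but not stated, the imagery arms retain a more adherent group and a completers-only comparison leans towards imagery. The combined arm is the most exposed, and item 6b says that arm is there partly to study intervention length.

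The Sample size section warns about attrition that changes the make-up of the sample, but allows for it only overall: 312 recruited to keep 260, never by arm.

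**Working it through.** **1. What the documents allow to be computed.** Loss between randomisation and T2 by arm cannot be derived. The number randomised is not stated, and 465 and 297 are totals over all arms. If the 297 are part of the 465, loss from T2 to T3 is 1 − 297/465 = 36.1%. That is after T2 and not by arm, so it says nothing about break-off during the exercise.

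**2. Formula for a completers-only bias.** Let an arm have true mean M, let a share p break off, and let quitters score δ lower than finishers, whose mean is F. Then M = (1 − p)F + p(F − δ) = F − pδ, so F = M + pδ. With no true effect (the same M in both arms), the finishers' contrast is:

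bias = δ × (p_imagery − p_control)

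**3. Illustration.** None of these inputs comes from the documents. Assume break-off of 2% in control, 10% in each single arm and 20% in the combined arm, with δ = 0.5 SD.

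| Contrast | Difference in break-off | Bias |
|---|---|---|
| Single vs control | 0.10 − 0.02 = 0.08 | 0.5 × 0.08 = 0.04 SD |
| Combined vs control | 0.20 − 0.02 = 0.18 | 0.5 × 0.18 = 0.09 SD |
| Each factorial main effect | (0.10 + 0.20)/2 − (0.02 + 0.10)/2 = 0.15 − 0.06 = 0.09 | 0.5 × 0.09 = 0.045 SD |
| Interaction | 0.20 − 0.10 − 0.10 + 0.02 = 0.02 | 0.5 × 0.02 = 0.01 SD |

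**4. Wider range.** With no break-off in control, 5% to 30% in an imagery arm and δ from 0.2 to 0.8 SD, the bias runs from 0.05 × 0.2 = 0.01 SD to 0.30 × 0.8 = 0.24 SD.

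**5. Effect of using T1.** Step 2 works on raw scores. If T1 enters with slope b, the bias becomes (p_imagery − p_control) × (δ_T3 − b·δ_T1). When finishers and quitters already differ at T1 in the same direction, this is smaller. In a change-from-T1 contrast (b = 1) with a stable gap it is zero, and only differential change remains. The figures in steps 3 and 4 are therefore upper values for such gaps.

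**6. The eligibility rule and the intention-to-treat plan side by side.** Item 18a would analyse everyone whatever they completed. Item 10 makes full completion a condition of being eligible. The same person can thus be inside the intention-to-treat set by one section and ineligible by the other. Item 18a also says no data will be missing, which cannot hold for people who break off or do not return at T3. It does not say which of its two analyses leads.

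**The case against.** The strongest reply is that an intention-to-treat analysis of all participants is already planned, so those who break off are not simply dropped, and the way missing values are filled may sit in an analysis plan that is not shown. The plan deserves that credit, and the filling method is not counted against it. The reply is not complete: the analysis is only additional, it is not named as the main one, and it conflicts with the eligibility rule.

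Other objections stand and limit the point.

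- **Item 11b.** A reader might infer that marking it not applicable is itself the error. It concerns criteria for discontinuing or modifying an allocated intervention, and rewriting it would not prevent voluntary break-off.
- **A forced writing task.** A reader might infer that imagery participants are made to write for 8 to 25 min. The times cover the whole exercise, 15–25 min applies to the combined arm only, and forced response is stated for questionnaire data, not expressly for the free-text box. The full exercise text is in a supplement, and the survey flow is not described.
- **Primary outcome.** Behaviour is recorded at T1 and T3 only, so missing T2 costs secondary outcomes. Loss of the primary outcome also requires that those who break off are not invited to T3, and the documents do not say whether they are.
- **Trial status.** A brief status note need not give counts by arm. Their absence limits what can be checked here and is not itself a defect.

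The Data quality screen of free-text responses is a separate exclusion and is not part of this calculation.

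**Conclusion.** The concern holds as a risk. Completion is made an eligibility criterion although it is observed only after randomisation, the burden before T2 is unequal by design, and the intention-to-treat analysis is neither given priority nor reconciled with that criterion.

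A reader might go further and conclude that quitters are in fact lost by arm and that the results are biased towards imagery. The documents do not show this: they give no break-off figures, and the direction depends on quitters being the less adherent people.

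Under the assumed rates the bias is about 0.04 SD for single and 0.09 SD for combined imagery against control on raw scores, about 0.045 SD in each factorial main effect and close to nothing in the interaction. It is less after accounting for T1 if the gap is already present there. For the T3 primary outcome it also needs those who break off to be missing at T3.

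**What to change.** 1. Remove questionnaire completion from Eligibility criteria {10}, and align the Participants section.
2. In item 18a, name the analysis of everyone randomised, in allocated arms, as the main comparison, with complete case as a sensitivity analysis.
3. Delete the statement that there will be no missing data.
4. Seek T3 responses from everyone randomised, whether or not the exercise or T2 was finished.
5. Report by arm the numbers randomised, breaking off before T2, and completing T2 and T3.

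Trial status says enrolment ended on 28 February 2021, and item 18a has email addresses destroyed once recruitment is completed. Change 4 is therefore chiefly for a repeat study. The analysis and reporting changes can still be applied here, the reporting as far as partial survey records were kept.

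The cost is wording and a participant flow table. The estimate becomes the effect of being offered imagery, may be slightly smaller, and relies on a stated way of handling missing T3 data.
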